## Abstract

**Background:**

Chronic obstructive pulmonary disease (COPD) leads to peripheral and respiratory muscle dysfunctions. Nowadays, inspiratory muscle training can be geared toward strength or endurance gains. This study aims to investigate the effects of an inspiratory muscle training (IMT) protocol using different therapeutic modalities to be implemented in pulmonary rehabilitation programs. The effects of IMT on exercise capacity were considered as the primary endpoint, and the effects of IMT on inspiratory muscle function, health-related quality of life, and daily physical activity level were considered as the secondary outcomes.

**Methods:**

This study is a blinded-investigator randomized controlled clinical trial. Sixty subjects will be randomly allocated into three groups: (1) pulmonary rehabilitation (PR) associated with inspiratory muscle training without any load (PRWIMT), (2) PR associated with inspiratory muscle training with a linear load (PRIMTLL), and (3) PR associated with inspiratory muscle training with isocapnic voluntary hyperpnea (PRIMTIVH). The protocol will be performed 5 days a week (3 days with supervision) for 10 weeks. The study will assess anthropometric data, lung function, respiratory muscle strength, and functional capacity by the Incremental Shuttle Walking Test and the Six-Minute Walk Test, lung volumes during the submaximal endurance test, peripheral muscle strength of the upper and lower limbs, dyspnea, and quality of life related to health, before and after the training protocol. Normality will be tested using the Kolmogorov-Smirnov test, and variables will be compared by two-way analysis of variance. The significance level was set at *p* < 0.05. Ethics approval was obtained from the Institutional Ethics Committee in Research (1.663.411). The study results will be disseminated through presentation at specific scientific conferences and publication in peer-reviewed journals.

**Discussion:**

The different IMT protocols used in our study will be able to guide respiratory therapists to understand and to include in conventional PR programs the most effective respiratory muscle training type in subjects with COPD.

**Trial registration:**

Brazilian Clinical Trials Registry, RBR-94v6kd. Registered on 11 March 2017.

**Electronic supplementary material:**

The online version of this article (10.1186/s13063-019-3271-1) contains supplementary material, which is available to authorized users.

## Strengths and limitations of the study

The study has the following strengths:The study is an investigator-blinded randomized controlled trial designed to aid in better understanding further effects that inspiratory muscle training (IMT) may add to conventional pulmonary rehabilitation (PR) programs.The subjects will be reevaluated after the protocol by an evaluator blinded to the intervention protocol allocation to describe the effects of different IMT modalities on exercise capacity.

One limitation of the study is that the training protocol will be partially performed at home by the studied subjects without clinical supervision.

## Background

Chronic obstructive pulmonary disease (COPD) is a chronic, preventable, and treatable disease that is characterized by persistent respiratory symptoms and airflow limitations; the primary triggering factor is significant long-term exposure to noxious particles or gases, which produce airway and/or alveolar airway changes [1]. The disease presents extrapulmonary manifestations such as skeletal muscle dysfunction, which is an important prognostic factor that justifies exercise intolerance in these patients [2].

In addition to pharmacological treatment, it is recommended that individuals with COPD take part in PR programs. Nowadays, PR is defined as an embracing intervention based on the complete evaluation of the patient followed by specific therapies that include but are not limited to training, education, and behavior changes, aiming to improve the physical performance and psychological status of individuals with chronic respiratory disease and to promote long-term adherence and behavior changes [3].

IMT may generate strength increase in patients with COPD; however, studies have shown that the training may overload these muscles when not well performed [4]. Although decades have passed with several studies about IMT in patients with COPD being conducted, there are still doubts regarding IMT efficiency and its influence on exercise tolerance in COPD subjects. Studies have shown that IMT does not determine exercise performance improvement in COPD, or that there is a weak correlation between respiratory muscle changes due to IMT and exercise performance [5].

The literature describes two modalities of respiratory muscle training: isocapnic voluntary hyperpnea, which consists of a training that requires the individual to perform voluntary hyperventilation during a certain period of time, maintaining an isocapnea [6]; and threshold valves of pressure loading, which require the individual to perform inspirations or expirations against resistance [7]. This device allows inspirations and expirations to be forced by the device, which causes selective strengthening of the respiratory muscles and mobilizes the entire rib cage. Studies show that therapy with isocapnic voluntary hyperpnea reduces dyspnea and improves exercise capacity and the quality of life of subjects [8]. Currently, the market has electronic IMT valves that seem to provide some benefits in relation to volume increase during training compared to mechanical valves; however, these effects have not yet been clinically demonstrated [9]. There have been, to date, disagreements over the effects of IMT in individuals with COPD [8].

Due to different results on the effect of IMT in COPD subjects, the aim of this study will be to investigate the effects of an IMT protocol to be included in PR programs. The first outcome will be the effects of the training on exercise capacity. Training on inspiratory muscle function (strength and resistance), state of health, and dyspnea level will be considered as secondary outcomes. We believe that the different protocols used in our study are able to guide physiotherapists with regard to the most effective type of IMT, as well as to elucidate the effects of IMT on exercise tolerance, to identify if there is any repercussion on strength and the resistance of the respiratory muscles when subjected to different training types. In addition, the best IMT modality can be included in conventional PR programs, allowing optimization of the therapeutic management of patients with COPD. One also hopes that these results will endorse adjustments to the modalities used to strengthen respiratory muscles, as we believe that a well-implemented therapeutic program can reduce morbidity/mortality rates in these individuals as well as improve their quality of life.

## Methods

### Study

This is a blinded randomized controlled clinical trial. The PR program will be performed by a respiratory therapist. Initial and final assessment will be performed by another previously trained respiratory therapist who will be blinded to the allocation groups in accordance with the Consolidated Standards of Reporting Trials (CONSORT) [10] and Standard Protocol Items: Recommendations for Interventional Trials (SPIRIT) [11].

### Subjects

Individuals with a clinical diagnosis of COPD according to the Global Initiative for Chronic Obstructive Lung Disease (GOLD) being treated at the Ambulatory Pulmonology department of University Hospital Onofre Lopes (HUOL)/Empresa Brasileira de Serviços Hospitalares (EBSERH) will be invited to participate in the study. All selected individuals will be assessed at the PneumoCardioVascular Lab HUOL/EBSERH to confirm disease stage. Patients in clinical follow-up with a specialized pulmonology physician and with use of adequate bronchodilation (modified Medical Research Council [mMRC] score ≥ 2/4), who are aged between 40 and 80 years, living in the city of Natal, RN/Brazil, not using oxygen therapy or presenting disease exacerbation in the last 3 months, and not practicing regular physical activity in the last 6 months will be eligible to participate. Subjects presenting musculoskeletal comorbidities that impair the subject’s gait, peripheral oxygen saturation (SpO_2_) < 90% during the Six-Minute Walk Test (6MWT), hypertensive subjects without control medication as well as those presenting with a hypertensive peak (> 140/90 mmHg) [12] for more than 3 consecutive days, those with an intellectual understanding impairment that interferes with the evaluation tests, or those who stop the therapeutic program, miss activity for more than 1 week, or miss reevaluation will be excluded from the study.

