### Study design

After recruitment, subjects will be invited to attend the PneumoCardioVascular and Respiratory Muscle Performance Laboratory HUOL/EBSERH to perform an initial evaluation. The assessment will be performed by a previously trained evaluator blinded to the intervention allocation group and will include anthropometry, lung function, respiratory muscle strength, exercise capacity, lung volumes associated with the submaximal endurance test, peripheral muscle strength (upper and lower limbs), dyspnea, and impact of COPD on a person’s life. After evaluation, a secure web-based randomization system (randomization.com) will be used to allocate subjects into three groups: the PRWIMT group will perform PR and IMT without any load; the PRIMTLL group will perform PR and IMT with a linear load, and the PRIMTIVH group will perform PR and IMT with isocapnic voluntary hyperpnea. The web-based randomization firstly generates a list of numbers from 1 to 60. These numbers are randomized into the study groups to which the subjects will be numerically allocated in order of arrival. After the intervention period, a blind evaluator to the intervention groups, as represented in Fig. 1, the flow diagram of the intervention protocols, will reevaluate all cases, according to the schedule of the study in Fig. 2. The SPIRIT checklist is provided as Additional file 1.

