#### Sample size

The sample size was calculated using two-way analysis of variance (ANOVA) for repeated measures by analyzing walking distance and the standard deviation in meters on the 6MWT from previously published data [15]. A two-tailed alpha error of 0.01 was implemented with a power of 95%, considering clinical improvement for COPD patients after PR and a difference of 30 m between groups on the walking test. For the calculations, the following means and standard deviations of the time observed in the 6MWT in the rehabilitation and control groups were used: pre-PR 312.43 ± 51.26 and post-PR 342.85 ± 48.82 m (rehabilitation group); pre-PR 305.13 ± 54.60 and post-PR 298.20 ± 52.81 m (control group), and a sample size of 32 subjects was found (effect size = 1.04). As the study of Elci et al. [15] was composed of two groups (rehabilitation and controls) and ours will be composed of three groups, we will assume that the 32 subjects will be part of the rehabilitation program (the PRIMTLL and PRIMTIVH groups), and 16 more subjects will be added as a study control group for a total sample of 48 subjects. In addition, 12 more subjects will be added into the study, because we will also assume a 20% loss to follow-up as well as 5% missing data, for a total sample size of 60 subjects.

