## Discussion

Literature data reporting the effects of respiratory muscle training regarding exercise tolerance are rare nowadays. We believe that the different protocols used in our study of high load and low load training will be able to guide respiratory therapists to the most effective respiratory muscle training type. Moreover, the study will elucidate the effects of IMT on exercise tolerance, identifying if there is any repercussion on both respiratory muscle static pressure and respiratory muscle strength when the patient is subjected to different efforts.

Finally, the best IMT modality may be included in conventional PR programs, thus optimizing the therapeutic management of COPD patients. We also hope that these findings endorse adjustments to the modalities used for respiratory muscle strengthening, as we believe that a well-implemented therapeutic program may reduce the morbidity/mortality rates for these individuals as well as improve their quality of life.

The protocol performance may show some limitations as individuals’ adherence and subjects’ access to the hospital will vary. Such limitations will be controlled by free specialized medical service and by the provision of a free bus pass allowing subjects to attend the interventions at the PR service. As clinical limitations we may highlight COPD exacerbation and/or other general clinical issues that may lead to a subject’s absence of 3 or more consecutive days or subjects being withdrawn from the study.

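### Three events that can occur only after randomisation are grounds for exclusion, so the rule as written leaves a comparison of completers and adherers exposed to attrition bias

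*Protocol article*

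**What the plan says.** The Subjects section of the protocol article gives one list of exclusions. It opens with conditions that can be checked at entry, such as gait-limiting comorbidity, desaturation on the Six-Minute Walk Test (6MWT) and uncontrolled hypertension. It ends with events during the trial: "those who stop the therapeutic program, miss activity for more than 1 week, or miss reevaluation will be excluded from the study".

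Study design fixes the order of events: "After evaluation, a secure web-based randomization system (randomization.com) will be used to allocate subjects into three groups". The same section says that, after the intervention period, a blinded evaluator "will reevaluate all cases, according to the schedule of the study in Fig. 2".

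The Sample size section reaches 48 patients ("16 more subjects will be added as a study control group for a total sample of 48 subjects") and then adds 12: "we will also assume a 20% loss to follow-up as well as 5% missing data, for a total sample size of 60 subjects".

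The Statistics analysis section names a two-way ANOVA with Bonferroni post hoc tests. It says nothing that would offset the exclusion rule. The Discussion lists, as a limitation, that exacerbation and other clinical issues may lead to "absence of 3 or more consecutive days or subjects being withdrawn from the study".

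**The concern.** Randomisation makes the three arms comparable at allocation. That holds at 10 weeks only if the patients compared are those who were allocated. Stopping, missing sessions and missing the post-test all happen after allocation and may depend on how well a patient tolerates the assigned training.

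All arms share the same treadmill, strength and education programme, but the added breathing training differs: 36 unloaded breaths (3 × 12), 36 breaths at a load rising from 35% to 80% of maximal inspiratory pressure, or up to 20 minutes of hyperpnoea in one-minute bouts. The Background notes that inspiratory training may overload these muscles when not well performed. The Discussion ties absence and withdrawal to exacerbation and other clinical problems. Exclusion could therefore relate both to arm and to prognosis, and blinding the assessor does not protect against that.

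The trial aims to identify the best modality for routine rehabilitation. That decision concerns everyone assigned to a modality, including those who cannot keep it up.

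**Working it through.** **Step 1. Timing.** Baseline evaluation, then allocation, then 10 weeks of training, then re-evaluation. A patient can stop the programme, miss its sessions or miss the re-evaluation only after allocation. All three are post-randomisation exclusions.

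**Step 2. The plan's own loss figure.** Base number 32 + 16 = 48. Allowing for 20% loss, 48 / (1 − 0.20) = 60; equally, 48 × 1.25 = 60. The stated total reproduces. Expected losses are 0.20 × 60 = 12 and, if the 5% missing data are counted as well, 0.25 × 60 = 15. That leaves 48 to 45 patients, or 16 to 15 per arm if allocation is equal (20 per arm, an assumption). The allowance restores the count; it does not address who is lost.

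**Step 3. How exclusion shifts the comparison.** Within an arm, let p be the share excluded and g the mean of retained patients minus the mean of excluded patients.

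- Retained mean − all-randomised mean = p × g
- With the same g in both arms, shift in the between-arm difference = (p₁ − p₂) × g

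The protocol gives neither p by arm nor g, so both are assumed. For g, take the gap in change between the two groups quoted in the Sample size section:

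- Rehabilitation: 342.85 − 312.43 = +30.42 m
- Control: 298.20 − 305.13 = −6.93 m
- g = 30.42 − (−6.93) = 37.35 m

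| Assumed exclusion, active vs control | g (m) | Shift (m) | Share of 30 m |
|---|---|---|---|
| 25% vs 10% | 37.35 | 0.15 × 37.35 = 5.6 | 19% |
| 30% vs 10% | 37.35 | 0.20 × 37.35 = 7.5 | 25% |
| 25% vs 15% | 37.35 | 0.10 × 37.35 = 3.7 | 12% |
| 25% vs 15% | 18.7 (half) | 0.10 × 18.7 = 1.9 | 6% |
| equal, same mechanism | any | 0 | 0% |

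**Step 4. What the shift means.** Suppose that in both arms retained patients change by +30.42 m and excluded patients by −6.93 m. The difference among retained patients is 0. Among all randomised patients, with 25% vs 10% excluded:

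- Active: 0.75 × 30.42 − 0.25 × 6.93 = 21.1 m
- Control: 0.90 × 30.42 − 0.10 × 6.93 = 26.7 m
- Difference: −5.6 m (−7.5 m at 30% vs 10%)

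On these inputs the retained-patient comparison hides a deficit in the active arm; it does not create an apparent gain.

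**Step 5. A second route.** Let exclusion correlate at r with a worse 6MWT. With SD = √((48.82² + 52.81²)/2) = 50.9 m, the retained mean rises by r × SD × φ(z_p)/(1 − p), where φ is the normal density and z_p the p-quantile. For r from 0.2 to 0.5:

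- 15% vs 25% loss: shift 1.5 to 3.8 m
- 10% vs 30% loss: shift 3.1 to 7.7 m
- outcome-related exclusion in one arm only, 20% to 30% loss: 3.6 to 12.6 m
- equal loss, same r: 0

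**The case against.** **The text says excluded from the study, not from the analysis, and an analysis plan not shown may define the analysis set.** This stands as to wording: the protocol nowhere says that data of withdrawn patients are discarded. But the point concerns a rule that the protocol states, not a gap. If exclusion ends follow-up, a patient removed for missing just over a week need not have the 10-week test, and no analysis plan can recover a measurement that was never made.

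**Differential loss is not shown.** This stands. The core programme is common to all arms, and the Discussion also names adherence and hospital access as sources of variation and offers free bus passes and medical care. Arm-related exclusion is plausible, not established.

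**The assumed inputs are unfavourable.** This stands too. The 37.35 m gap compares rehabilitated with non-rehabilitated patients, whereas someone excluded for a short absence may have completed most of the training.

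Stronger readings that the documents do not support:

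- *The hardest arm will look better than it is, by a known amount.* Step 4 shows that the same inputs can mean a hidden deficit, and equal loss gives zero. Neither sign nor size can be derived.
- *The plan expects 15 exclusions.* It adds 12 patients and lists 5% missing data separately, so 15 is only the upper end.
- *The Discussion sets a second absence threshold.* It names an absence of 3 or more days and withdrawal as alternative consequences of clinical problems. It states no exclusion rule.
- *Study design flatly contradicts Subjects.* The phrase "will reevaluate all cases" sits in a sentence about who assesses and may mean only that the assessor is blinded. The two sections need reconciling, no more.

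**Conclusion.** The concern holds as exposure to bias. The protocol lists three post-randomisation events as grounds for exclusion and, followed as written, compares completers and adherers rather than the groups as randomised. This rests on the stated rule and the stated order of events, not on a calculation.

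The loss concerned is 12 to 15 of 60 patients on the plan's own allowance. Any bias is of unknown size and direction. The figure of 5.6–7.5 m (19–25% of the 30 m target) depends on assumed exclusion shares of 25–30% versus 10% and an assumed 37.35 m gap. Milder assumptions give 1.9–3.7 m, and equal loss by the same mechanism gives 0.

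**What to change.** - Remove the three events from the exclusion criteria in the Subjects section. Describe them as discontinuation of, or non-adherence to, the intervention.
- State that every randomised patient is invited to the 10-week assessment already scheduled, whether or not training was completed. Reconcile Subjects with Study design on who is re-evaluated.
- Make the primary comparison by allocated arm in all randomised patients. Handle missing post-tests with a likelihood-based model or multiple imputation that uses the baseline 6MWT.
- Use the adherence rule only to define a secondary per-protocol set, and report the numbers and reasons for non-completion by arm.

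The cost is a change of wording and some effort to recall patients who have stopped. The estimate in all randomised patients may be somewhat diluted relative to the one in completers. The change should be made while post-tests can still be obtained.

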### Study design

After recruitment, subjects will be invited to attend the PneumoCardioVascular and Respiratory Muscle Performance Laboratory HUOL/EBSERH to perform an initial evaluation. The assessment will be performed by a previously trained evaluator blinded to the intervention allocation group and will include anthropometry, lung function, respiratory muscle strength, exercise capacity, lung volumes associated with the submaximal endurance test, peripheral muscle strength (upper and lower limbs), dyspnea, and impact of COPD on a person’s life. After evaluation, a secure web-based randomization system (randomization.com) will be used to allocate subjects into three groups: the PRWIMT group will perform PR and IMT without any load; the PRIMTLL group will perform PR and IMT with a linear load, and the PRIMTIVH group will perform PR and IMT with isocapnic voluntary hyperpnea. The web-based randomization firstly generates a list of numbers from 1 to 60. These numbers are randomized into the study groups to which the subjects will be numerically allocated in order of arrival. After the intervention period, a blind evaluator to the intervention groups, as represented in Fig. 1, the flow diagram of the intervention protocols, will reevaluate all cases, according to the schedule of the study in Fig. 2. The SPIRIT checklist is provided as Additional file 1.

**Fig. 1 Fig1:**
[figure not shown]
Flow diagram of intervention protocols

**Fig. 2 Fig2:**
[figure not shown]
Schedule of the study

### Intervention

#### Pulmonary rehabilitation program and respiratory muscle training

The PR protocol will be performed three times a week for 10 consecutive weeks. All activities will be supervised by a previously trained respiratory therapist in a room with a controlled temperature set between 23 and 26 °C. All individuals will be instructed to perform the rehabilitation program 5 days a week — 3 days with supervision and 2 without supervision — for at least one hour a day, according to the recommendations of the guideline on PR in adults [13]. Subjects will receive orientation to fill in the unsupervised exercise diary regarding type of exercise, duration, and frequency as well as for symptoms referenced during the activity using the modified Borg scale (from 4 to 6) to limit the intensity of the exercise [14].

All three groups will submit to a conventional rehabilitation program consisting of aerobic exercise on a treadmill. For the first week, the subjects will perform 20 min of activity. A resting period lasting 2 min maximum will be allowed whenever requested by the subject. The training time will be increased after the 5th week to reach 30 min of daily activity [15]. Aerobic exercise will be performed on a treadmill, with a velocity corresponding to 70% of the maximum velocity achieved in the Incremental Shuttle Walking Test (ISWT) [16]. Ten percent of the starting time (2–3 min) of the training will be at a speed of 40% of the maximum speed reached in the ISWT for heating, 80% of the training time (17–25 min) will be at the target speed (70% ISWT), and the remaining 10% of the time will be cooling, with the same speed as for heating, reducing the speed to zero at the end of the training period [17, 18]. The physical activity training will be interrupted whenever the degree of dyspnea sensation reaches 4–6 (intense) on the Borg scale [14] or the heart rate (HR) exceeds 85% of the individual maximum HR value (220 – age). If the saturation drops (SpO_2_ < 90%) [19] during the exercise, we will administer supplemental oxygen at minimal flow with a nasal cannula to maintain higher than 90% saturation. The patients will be monitored every 5 min. Participants will be instructed to maintain aerobic activities on days that they are not performing the supervised PR program. Strength training for lower and upper limb muscles will be performed through a program consisting of 3 sets of 12 repetitions, initially using 60% of 1 maximal repetition (1RM), and this load will be increased to 70% by the 5th week and 80% in the 8th week of training [20]. For the upper limbs the training will be directed to the biceps, triceps, pectoral, and deltoid muscles, and for the lower limbs, the training will be for quadriceps and triceps femoris [3]. Guidance in energy conservation techniques as well as educational speeches regarding self-management of the disease will be provided [13]. The PRWIMT group will perform PR and IMT without any load; the PRIMTLL group will perform PR and IMT with a linear load; the PRIMTIVH group will perform PR and IMT with isocapnic voluntary hyperpnea.

